# Azithromycin to prevent acute lower respiratory infections among Australian and New Zealand First Nations and Timorese children (PETAL trial): study protocol for a multicentre, international, double-blind, randomised controlled trial

**DOI:** 10.1136/bmjopen-2024-097455

**Published:** 2025-02-05

**Keywords:** Respiratory infections, Antibiotics, Child, Paediatric thoracic medicine, Randomized Controlled Trial

## Abstract

**Introduction:**

Acute lower respiratory infections (ALRIs) remain the leading causes of repeated hospitalisations among young disadvantaged Australian and New Zealand First Nations and Timorese children. Severe (hospitalised) and recurrent ALRIs in the first years of life are associated with future chronic lung diseases (eg, bronchiectasis) and impaired lung function. Despite the high burden and long-term consequences of severe ALRIs, clinical, evidence-based and feasible interventions (other than vaccine programmes) that reduce ALRI hospitalisations in children are limited. This randomised controlled trial (RCT) will address this unmet need by trialling a commonly prescribed macrolide antibiotic (azithromycin) for 6–12 months. Long-term azithromycin was chosen as it reduces ALRI rates by 50% in Australian and New Zealand First Nations children with chronic suppurative lung disease or bronchiectasis. The aim of this multicentre, international, double-blind, placebo-containing RCT is to determine whether 6–12 months of weekly azithromycin administered to Australian and New Zealand First Nations and Timorese children after their hospitalisation with an ALRI reduces subsequent ALRIs compared with placebo. Our primary hypothesis is that children receiving long-term azithromycin will have fewer medically attended ALRIs over the intervention period than those receiving placebo.

**Methods and analysis:**

We will recruit 160 Australian and New Zealand First Nations and Timorese children aged <2 years to a parallel, superiority RCT across four hospitals from three countries (Australia, New Zealand and Timor-Leste). The primary outcome is the rate of medically attended ALRIs during the intervention period. The secondary outcomes are the rates and proportions of children with ALRI-related hospitalisation, chronic symptoms/signs suggestive of underlying chronic suppurative lung disease or bronchiectasis, serious adverse events, and antimicrobial resistance in the upper airways, and cost-effectiveness analyses.

**Ethics and dissemination:**

The Human Research Ethics Committees of the Northern Territory Department of Health and Menzies School of Health Research (Australia), Health and Disability Ethics Committee (New Zealand) and the Institute National of Health-Research Technical Committee (Timor-Leste) approved this study. The study outcomes will be disseminated to academic and medical communities via international peer-reviewed journals and conference presentations, and findings reported to health departments and consumer-based health organisations.

**Clinical trial registration:**

Australia New Zealand Clinical Trial Registry ACTRN12619000456156.

STRENGTHS AND LIMITATIONS OF THIS STUDYThe randomised controlled trial is multicentre, involving three countries.Standardised methods from our previous azithromycin trials will be used.Outcome measures are clinically relevant and clearly defined.The trial is powered to address the primary and secondary objectives.A potential limitation that may affect attrition is the duration of follow-up for 24 months.

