The importance of reducing recurrent ALRIs among children hospitalised previously is reflected in data from studies involving children from settings where the burden of acute and chronic lung disease is particularly high.^2^ A prospective cohort study of First Nations children with either chronic suppurative lung disease (CSLD) or radiographic-confirmed bronchiectasis from Alaska, Australia and New Zealand found at baseline these children had an earlier onset and higher frequency of ALRIs than their local First Nations populations.^10^ Our previous RCTs^14 15^ that included 162 Northern Territory First Nations children aged <2 years hospitalised with bronchiolitis reported 41 children (25%) were rehospitalised with a respiratory illness within 6 months of hospital discharge. Furthermore, 30/157 (19%) had developed bronchiectasis by 13 months (IQR, 7–18) post-hospitalisation.^16^ In New Zealand, a study among 94 First Nations children aged <2 years found 74% had ongoing respiratory morbidity (ie, cough, chest X-ray changes) 12 months after an ALRI hospitalisation.^17^ This included three children diagnosed with bronchiectasis post-hospitalisation by chest high-resolution CT (HRCT) scans undertaken for clinical reasons.

One feasible, but untested, intervention to reduce recurrent ALRIs is prescribing long-term oral azithromycin, an antimicrobial agent with immunomodulatory and anti-inflammatory properties.^18^ Azithromycin is well tolerated and its half-life of 70 hours allows infrequent dosing regimens (eg, once per week) that reduces the burden on families. Our previous randomised controlled trial (RCT) among First Nations children from Australia and New Zealand with CSLD and bronchiectasis found weekly azithromycin for up to 24 months halved respiratory exacerbation rates while receiving the active treatment.^19^ Children who received azithromycin were also less likely to be hospitalised for respiratory illness during this period.^19^ RCTs in adults^20^ and subsequent trials by other groups that included children also found similar effects. For example, long-term azithromycin for 6 months reduced exacerbation rates by 55% among children and young adults with primary ciliary dyskinesia^21^ and also by a similar margin in Southern African children with HIV-associated chronic lung disease.^22^ Nevertheless, despite these positive results, concerns remain over the selection of macrolide-resistant pathogens associated with long-term azithromycin.^23 24^

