## Methods and analysis

### Design

The azithromycin to **‘**Prevent rEcurrenT Acute Lower Respiratory Infections’ (PETAL) trial is a parallel (1:1), double-blind, placebo-controlled, multicentre, international superiority RCT (figure 1). It aims to determine whether 6–12 months of azithromycin following ALRI hospitalisation reduces subsequent ALRIs and improves other clinical and economic outcomes. The first participant was randomised in October 2020, and we anticipate that recruitment will be completed by February 2025.

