##### Sample size

Based on our primary outcome (rate of medically attended ALRI), 80 children per group (total sample size n=160, including 15% attrition) will provide 90% power to detect a 40% reduction (IRR=0.6) in medically attended ALRI episodes per child-year. We assumed a rate of three medically attended ALRI episodes per child-year in the control group, based on community presentations for respiratory illnesses in our setting,^33^ a shape parameter of k=0.4, and a two-sided significance level of 5%. Children who are withdrawn or lost to follow-up (at 6–12 months) will be replaced until the required sample size is obtained. Our previous bronchiectasis RCT^19^ reported a halving of respiratory exacerbations in the azithromycin group and the maximal benefit was achieved between 4 and 14 months of the intervention.^34^

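### The article says the trial is powered for its secondary objectives, but it was sized on the primary outcome alone, and power for on-treatment ALRI hospitalisation is about 41-56% under its own background figure

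*Protocol article*

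**What the plan says.** The strengths and limitations box, printed after the trial registration number, states: "The trial is powered to address the primary and secondary objectives". It makes no exception for any secondary objective.

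The Sample size section opens "Based on our primary outcome (rate of medically attended ALRI" and goes on to say that "80 children per group (total sample size n=160, including 15% attrition) will provide 90% power" for a 40% reduction (IRR 0.6). Its inputs are specific to that outcome: "We assumed a rate of three medically attended ALRI episodes per child-year in the control group", a shape parameter of 0.4 and a two-sided 5% level. It adds that children who withdraw or are lost will be replaced. No control rate, effect size, dispersion or power is given for any secondary outcome.

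The Outcomes section lists ALRI hospitalisation during the intervention, and again to 24 months, as secondary outcomes. Aims and hypotheses includes a reduction in hospitalised ALRIs among the secondary hypotheses. The one post-discharge hospitalisation figure is in the Introduction, where the sponsor's earlier bronchiolitis trials "reported 41 children (25%) were rehospitalised with a respiratory illness within 6 months of hospital discharge".

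**The concern.** A claim of power for an outcome needs an event rate, an effect and a sample size that fit together. Here they are given only for an outcome assumed to occur three times per child-year. A 25% six-month risk of rehospitalisation corresponds to roughly 0.6 events per child-year, about one fifth of that. With the same children and the same relative effect, information on hospitalisation must be much lower.

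The stake is interpretation. Hospitalisation is a stated secondary hypothesis, and savings in hospitalisations and medical evacuations enter the cost-effectiveness outcome. If the trial is presented as powered for this outcome, a wide interval that includes 1 could be taken to show that azithromycin does not reduce admissions. The article itself says that off-label use is already frequent, so such a reading would matter.

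**Working it through.** **1. Reproduce the stated size.** Inputs from Sample size and Design: control rate r0 = 3 per child-year, IRR = 0.6 (r1 = 1.8), k = 0.4, two-sided 5%, 90% power, 1:1 allocation, 15% attrition. Follow-up is taken as t = 1 year, because Choice of duration of intervention reports that only 2% have opted out at 6 months.

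Variance term: V = 1/(t·r0) + 1/(t·r1) + 2k = 0.333 + 0.556 + 0.800 = 1.689.

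n = (1.960 + 1.2816)² × V / (ln 0.6)² = 10.507 × 1.689 / 0.2609 = 68.0 per arm, and 68.0/0.85 = 80.0. The stated 80 per arm reproduces.

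**2. Control rate for hospitalisation.** Set the probability of at least one event by 6 months to 25%.
- Poisson (k = 0): r0 = −2 ln 0.75 = 0.575 per year.
- Negative binomial: r0 = 2(0.75^(−k) − 1)/k, which is 0.610 for k = 0.4 and 0.667 for k = 1.

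**3. Power for the on-treatment hospitalisation rate.** Power = Φ(|ln IRR|·√(n/V) − 1.960), with t = 1. Both 68 per arm (15% lost) and 80 per arm (all dropouts replaced) are shown.

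| k | r0 per year | V at IRR 0.6 | IRR 0.6, n = 68 | IRR 0.6, n = 80 | IRR 0.5, n = 68 | IRR 0.5, n = 80 |
|---|---|---|---|---|---|---|
| 0 | 0.575 | 4.635 | 49.9% | 56.4% | 70.7% | 77.5% |
| 0.4 | 0.610 | 5.173 | 45.7% | 51.9% | 66.6% | 73.6% |
| 1 | 0.667 | 6.000 | 40.5% | 46.2% | 61.1% | 68.1% |

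Example for k = 0.4, n = 68: 0.5108 × √(68/5.173) = 1.852; 1.852 − 1.960 = −0.108; Φ = 0.457.

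For 90% power at IRR 0.6, the formula in step 1 gives 187 (k = 0) to 242 (k = 1) evaluable children per arm.

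Analysed as a proportion with any admission over 12 months (normal approximation, pooled variance under the null), power is 29-42% with 68 per arm and 33-48% with 80.

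**4. How far the control rate would have to move.** For 80% power at IRR 0.6 with 80 per arm, V must be at most 80 × 0.2609/(1.960 + 0.8416)² = 2.66. Since V = 2.667/r0 + 2k, r0 must be about 1.0 per year (k = 0) or 1.4 (k = 0.4), around twice the rate in step 2. In the other direction, the highest infant hospitalisation rate in the Introduction, 427 per 1000, gives 36-39% with 68 per arm (k = 0.4 to 0).

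**5. Hospitalisation to 24 months.** Same formula with t = 2 and a constant control rate.
- 40% reduction persisting for the year off treatment (IRR 0.6): 56-79% with 68 per arm, 63-85% with 80.
- 40% reduction in year 1 and none in year 2, so overall IRR = (0.6 + 1.0)/2 = 0.8: 16-26% with 68 per arm, 18-30% with 80.

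**6. Chronic-symptom composite at 24 months.** For a 40% relative reduction, unpooled normal approximation and 68 per arm, a control proportion of 67% against 40.2% gives 0.268/√(0.4615/68) = 3.25, so power is about 90%. At 74%, the proportion with ongoing morbidity at 12 months in the New Zealand cohort in the Introduction, power is about 96%.

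**The case against.** **The hospitalisation inputs are borrowed.** The article states no effect size or dispersion for this outcome. The 25% comes from Northern Territory children with bronchiolitis and counts any respiratory illness. PETAL also enrols pneumonia cases and children in New Zealand and Timor-Leste, and selects for severity or a recent earlier admission. The control rate could be higher or lower. This stands, and it is why the power is given as a conditional range. It does not restore the claim: the control rate would have to be near double, or the effect larger than a halving, for on-treatment hospitalisation to reach 80%.

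**Dropouts are to be replaced.** This also stands, so 80 evaluable per arm is shown beside 68.

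**A fuller protocol might hold secondary power calculations.** Their absence from an article is no fault in itself. The point is the article's positive statement, set against a sample size that matches the primary outcome and that falls short for on-treatment hospitalisation on the article's own background figure.

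**The analysis already reports intervals.** Clinical outcomes specifies IRRs with 95% CIs for hospitalisation, so part of the safeguard is in place. What is missing is a statement of how an inconclusive interval will be read.

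**A reader might infer that every secondary outcome is underpowered.** The documents do not support that. The composite could be well powered if its control proportion is about 67% or more, and hospitalisation to 24 months can exceed 80% in the most favourable case. Nor can a low power be quoted for bronchiectasis from the 19% in the Introduction: HRCT-confirmed bronchiectasis alone is not a listed outcome, and scans are not routine.

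**Conclusion.** The statement in the strengths box is wrong as written. The sample size itself is not: 80 per arm reproduces for the primary outcome.

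For the on-treatment ALRI hospitalisation rate, power is about 41-50% with 68 evaluable per arm and 46-56% with 80. This assumes 25% of controls rehospitalised by 6 months, a 40% reduction, a 12-month intervention and dispersion from 0 to 1. None of the 50% reduction scenarios reaches 80%.

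These figures should not be carried over to the 24-month hospitalisation outcome, where power depends mainly on whether the effect lasts after treatment stops. No shortfall is claimed for the chronic-symptom composite. That the claim is unsupported does not depend on the exact percentages.

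**What to change.** - Replace the sentence in the strengths and limitations box with: 'The trial is powered for the primary outcome.'
- Under Sample size, state the achieved power or the detectable rate ratio for on-treatment ALRI hospitalisation, with the assumed control rate, dispersion, follow-up and evaluable number.
- State that a non-significant hospitalisation result will be interpreted from its 95% CI and not as evidence of no effect.

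The cost is wording. One advertised property becomes less favourable. No extra children are needed, and the design and the primary analysis stay as they are.

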## Introduction

 Acute lower respiratory infections (ALRIs (including bronchiolitis and pneumonia)), remain the most common global cause of child morbidity and mortality beyond the neonatal period.^1^ In 2021, there were an estimated 37.8 million ALRIs worldwide resulting in 502 000 deaths in children aged <5 years.^2^ The greatest burden was in children from low- and middle-income countries (LMICs) where 98.4% of ALRIs and 99.8% of deaths occurred.^2^ For example, in Timor-Leste, a LMIC, the ALRI incidence and its associated mortality in 2021 was 48 and 1.31/1000 children aged <5 years, respectively, compared with 11 and 0.3/1000 children aged <5 years in high-income countries, respectively.^2^ Nevertheless, there is also a high disease burden in disadvantaged First Nations children in high-income countries, especially during infancy where ALRI hospitalisation rates in the USA,^3^ Australia^4^ and New Zealand Māori and Pacific infants are 116, 427, 131, and 187/1000 infants aged <12 months, respectively.^5^

Severe (hospitalised) and recurrent ALRIs in the first years of life when the lungs are developing and vulnerable to injury are associated with future impaired lung health,^6^ reduced lung function trajectories^7 8^ and subsequent increased risk of chronic lung diseases (eg, bronchiectasis and chronic obstructive pulmonary disease (COPD)).^9^,^11^ Aboriginal and Torres Strait Islanders, and New Zealand Māori, and Pacific Islanders (henceforth referred to as First Nations), and Timorese children are at high risk of recurrent ALRIs,^4 6^ and in First Nations people chronic lung disease.^6 12^ Despite the high burden and long-term consequences of severe ALRIs, there are limited, clinically feasible strategies except national immunisation programmes, which include influenza and/or pneumococcal and *Haemophilus influenzae* type b conjugate vaccines^13^ that reduce the risk of both ALRI hospitalisations and recurrent ALRIs in young children.

The importance of reducing recurrent ALRIs among children hospitalised previously is reflected in data from studies involving children from settings where the burden of acute and chronic lung disease is particularly high.^2^ A prospective cohort study of First Nations children with either chronic suppurative lung disease (CSLD) or radiographic-confirmed bronchiectasis from Alaska, Australia and New Zealand found at baseline these children had an earlier onset and higher frequency of ALRIs than their local First Nations populations.^10^ Our previous RCTs^14 15^ that included 162 Northern Territory First Nations children aged <2 years hospitalised with bronchiolitis reported 41 children (25%) were rehospitalised with a respiratory illness within 6 months of hospital discharge. Furthermore, 30/157 (19%) had developed bronchiectasis by 13 months (IQR, 7–18) post-hospitalisation.^16^ In New Zealand, a study among 94 First Nations children aged <2 years found 74% had ongoing respiratory morbidity (ie, cough, chest X-ray changes) 12 months after an ALRI hospitalisation.^17^ This included three children diagnosed with bronchiectasis post-hospitalisation by chest high-resolution CT (HRCT) scans undertaken for clinical reasons.

One feasible, but untested, intervention to reduce recurrent ALRIs is prescribing long-term oral azithromycin, an antimicrobial agent with immunomodulatory and anti-inflammatory properties.^18^ Azithromycin is well tolerated and its half-life of 70 hours allows infrequent dosing regimens (eg, once per week) that reduces the burden on families. Our previous randomised controlled trial (RCT) among First Nations children from Australia and New Zealand with CSLD and bronchiectasis found weekly azithromycin for up to 24 months halved respiratory exacerbation rates while receiving the active treatment.^19^ Children who received azithromycin were also less likely to be hospitalised for respiratory illness during this period.^19^ RCTs in adults^20^ and subsequent trials by other groups that included children also found similar effects. For example, long-term azithromycin for 6 months reduced exacerbation rates by 55% among children and young adults with primary ciliary dyskinesia^21^ and also by a similar margin in Southern African children with HIV-associated chronic lung disease.^22^ Nevertheless, despite these positive results, concerns remain over the selection of macrolide-resistant pathogens associated with long-term azithromycin.^23 24^

In contrast, data for treating virus-associated ALRIs are less convincing. We previously found azithromycin given for up to 3 weeks to treat a single episode of bronchiolitis in Australian and New Zealand First Nations children did not improve short-term outcomes (hospitalisation or wheeze by 6 months).^14 15^ A recent systematic review and meta-analysis involving seven RCTs reported azithromycin did not provide any meaningful clinical benefit in children aged <2 years hospitalised with bronchiolitis and did not reduce subsequent wheezing episodes.^25^

Despite the current lack of evidence for long-term azithromycin in children hospitalised previously for an ALRI, it is often prescribed in the Northern Territory of Australia. For example, our prospective study of children undergoing evaluation for chronic cough at Royal Darwin Hospital revealed 27% of 304 children (88% First Nations, median age 2.3 years (IQR 1.5–3.8)) had received long-term azithromycin before bronchiectasis was confirmed by chest HRCT scans.^26^ Furthermore, it is unknown how many children are prescribed azithromycin routinely in primary healthcare settings for a chronic cough without referral for appropriate investigations. In our follow-up study of 162 Northern Territory children hospitalised previously for bronchiolitis,^16^ 43 (26%) were receiving long-term azithromycin prescribed by their general paediatrician for recurrent ALRIs.

In summary, young children in disadvantaged First Nations and LMIC populations have a large ALRI disease burden. This is when lungs are most susceptible to injury, leading to future impaired lung growth and function and subsequent chronic lung diseases. An intervention to prevent ALRIs during this critical phase of lung development may have both short- and long-term benefits. Following its success in clinical trials, long-term (>6 months) azithromycin is now recommended for preventing exacerbations in bronchiectasis.^27^ Despite lacking robust clinical data, there is also frequent ‘off-label’ use of azithromycin for chronic or recurrent respiratory symptoms, including ALRIs, in some communities noted for their high risk of CSLD and bronchiectasis. Taken together, there is an urgent need for high-quality RCTs to determine whether long-term azithromycin in young children following an ALRI hospitalisation is safe and efficacious at preventing further ALRIs when living in settings where a high burden of chronic lung disease and risk for future lung impairment exists.

## Aims and hypotheses

The primary aim of this RCT is to determine whether 6–12 months of weekly azithromycin (compared with placebo) following hospitalisation for an ALRI reduces the rate of subsequent episodes in First Nations and Timorese children aged <2 years. Our primary hypothesis is that children receiving long-term azithromycin will have fewer medically attended ALRIs over the intervention period than those receiving placebo.

Our secondary aims are to determine the effect of 6–12 months of weekly azithromycin (compared with placebo) on the rates and proportions of participants with ALRI-related hospitalisations, adverse events, nasopharyngeal carriage and antimicrobial resistance of respiratory pathogens and subsequent chronic respiratory symptoms/signs suggestive of underlying CSLD or bronchiectasis at 24 months. We will also assess the cost-effectiveness of the intervention by collecting healthcare-related costs and calculating the incremental cost-effectiveness ratio (ICER) on the potential benefits of azithromycin on hospitalisation, medical evacuations and other associated costs to health services compared with placebo.

Our secondary hypotheses are that 6–12 months of weekly azithromycin will result in reduced hospitalised ALRI episodes and reduced chronic respiratory symptoms/signs suggestive of underlying CSLD or bronchiectasis at 24 months, will be safe and will provide health economic benefits to health services, but with increased antimicrobial resistance in nasopharyngeal respiratory pathogens.

